### Data confidentiality and storage

All team members will be trained in HIPAA and safe data handling practices. To maintain patient confidentiality and privacy, the data will be maintained on a password-protected secure server and using the secure, password-protected REDCap platform.

### Data and safety monitoring plan

The principal investigator (PI) is responsible for this project’s conduct and shall ensure that all work and services described, or incidental to those described, are conducted following accepted standards of medical practice. The PI and co-investigators will maintain all master subject lists, and all data collected will be maintained in a password-protected secure server and reviewed at regular intervals to ensure adherence to the investigational procedures outlined in the protocol.

The approved research team members will obtain information regarding the patient’s lifestyle and demographic habits. Data will be accepted from primary care clinic records and charts. Each data abstractor will use a pre-formulated data collection tool to enhance the uniformity of information. Statistical analysis for inter-observer variability will be conducted on a subset of duplicate charts to ensure the quality of the data abstracted and used for the study.

Meetings will be held at regular intervals to discuss data management, general IRB compliance, and other study aspects and to analyze the collected data. The PI will evaluate data quality and ensure that data evaluation is performed frequently. All data will be documented and retained in the study files.

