**Outcomes:**

The primary outcome is index-visit Lifestyle Readiness and Confidence to Change scores. Secondary outcomes include satisfaction with the clinic visit, intention to change specific lifestyle behaviors, and healthcare use outside the clinic at 30 days and 6 months, as assessed via record review. A 3–12-month follow-up survey will assess self-reported lifestyle changes and new diagnoses.

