## Materials and methods

This will be a randomized, controlled, unblinded, two-armed superiority clinical trial. The study will be conducted according to the Standard Protocol Items: Recommendations for Interventional Trials (SPIRIT) Checklist (see S5 Checklist SPIRIT Checklist). The study was approved by Trinity Health at Ann Arbor Institutional Review Board (IRB number: E-24–1117). The trial was prospectively registered in the Clinicaltrials.gov database (registration number: NCT06730737).

The study’s primary outcome will be the results from the Lifestyle Readiness to Change and Confidence to Change questionnaires, both of which use a *readiness ruler* (see S2 Appendix B) [12]. The intervention will include four primary prevention domains promulgated by the American College of Lifestyle Medicine: diet, exercise, sleep hygiene, and smoking cessation.

Secondary aims include:

1)To evaluate the ability to implement a preventive education strategy in the primary care clinic setting2)To assess the impact of age on willingness to change lifestyle behaviors3)To determine characteristics of those receiving the video concerning patient satisfaction, utilizing select Hospital Consumer Assessment of Healthcare Providers and Systems (HCAHPS) Survey questions, compared to the control group

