### Study procedures

Research associates and/or research team members will screen for eligible patients using a screening form based on the inclusion/exclusion criteria mentioned above. Results will be analyzed at two stages: first, with the results of the questionnaires administered as part of the initial visit, and second, after concluding the 3–12 month follow-up survey. The consent, educational video, and questionnaire will all be conducted while the patient is in the waiting room, after the clinician (physician or advanced practice provider) has completed the initial patient encounter, or after the provider contact has been completed.

The patients will fill out the composite questionnaire. This questionnaire is designed with the following criteria: prioritize using validated tools capable of self-administration. The Readiness-to-Change questionnaire evaluates patient readiness to implement ten lifestyle behaviors based on a 5-point rating scale. A rating of 5 represents having no interest in the suggested lifestyle change, which is consistent with the precontemplation stage of the transtheoretical model (TTM). A rating of 4 means an interest in implementing the lifestyle change in the next few months (contemplation stage of the TTM). A rating of 3 represents having the plan to implement the lifestyle change within the next month (preparation stage of the TTM). A rating of 2 represents having already started the lifestyle change within the past few months (action stage of TTM). A rating of 1 means having maintained lifestyle behavior changes for over 6 months (maintenance stage of TTM). The Confidence-to-Change questionnaire evaluates patient confidence in implementing the same lifestyle behaviors as the Readiness-to-Change questionnaire. However, the Confidence-to-Change questionnaire is based on a 3-point rating scale. Ratings are as follows: 3-very confident, 2-somewhat confident, and 1-not very confident [12]. The Confidence-to-Change questionnaire addresses any barriers or hesitancy that may impact patient confidence in implementing better lifestyle behaviors. Additional questions will include measures of satisfaction taken from the HCAHPS, specifically addressing their practitioner and visit (S2 Appendix B).

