### Participant privacy

Subject confidentiality will be maintained using a randomly generated participant identification number/code. The participant identification number will be stored with the patient’s identifying information, such as name and room number, for verification purposes. Identifying information will be kept in a password-protected, secure REDCap file on a password-protected server. Such information will only be accessible to the research team trained in research ethics (CITI training) and HIPAA compliance.

Using personally identifiable data is necessary to determine eligibility, abstract chart data, and follow up with patients. All patient information collected will be stored in a password-protected secure server using REDCap and only accessed when necessary by authorized research associates.

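### Chart abstractors are not masked to arm, and the stated form and duplicate-chart agreement check cannot reveal a lean shared by both readers, so the record-review healthcare-use outcome is open to avoidable bias

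*Protocol article*

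**What the plan says.** - **Blinding.** Materials and methods: "This will be a randomized, controlled, unblinded, two-armed superiority clinical trial". No role is described as masked.
- **Outcome.** The abstract's Outcomes paragraph lists among the secondary outcomes "healthcare use outside the clinic at 30 days and 6 months, as assessed via record review".
- **Who handles the data.** The Data and safety monitoring plan begins: "The approved research team members will obtain information regarding" lifestyle and demographic matters. It goes on to accept data from clinic records and charts. Participant privacy says identifiable data are needed for chart abstraction and are "only accessed when necessary by authorized research associates".
- **What else those roles do.** Study procedures: "Research associates and/or research team members will screen for eligible patients". Elsewhere in the article, team members may start the video, help with the questionnaire and make the follow-up contact.
- **Safeguards.** The Data and safety monitoring plan names two. The first is a form: "Each data abstractor will use a pre-formulated data collection tool to enhance the uniformity of information". The second is a duplicate reading: "Statistical analysis for inter-observer variability will be conducted on a subset of duplicate charts to ensure the quality of the data abstracted".
- **Other sources.** Study procedures and Statistical methods add that a data-analytics group helps to produce the comorbidity index and other record information. It is not said to supply healthcare use.

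**The concern.** Two abstractors who both know the arm can agree on every chart and still both search one arm's notes less hard, or apply a different threshold for what counts as use outside the clinic. A form fixes which fields are filled in. It does not fix how hard someone looks, and it does not hide the arm. Agreement statistics measure how far two readings differ from each other, not how far both differ from the truth.

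The clinic survey and the follow-up call are answered by patients who know whether they saw a video, so those outcomes cannot easily be assessed blind. Healthcare use from the record can be. If the arm is known when charts are read, a difference in recorded use could reflect how the charts were read, and the planned quality check would not show it.

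**Working it through.** The plan gives no figure to reproduce for this outcome: no event rate, no capture rate and no allocation ratio. The check has two parts.

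**1. The sections side by side.** The trial is unblinded. The roles that screen, start the video, assist with questionnaires and follow up overlap with the roles that work with identifiable chart data. Allocation is done in REDCap, which also holds the link from study ID to patient. No section separates abstraction from allocation. Knowledge of the arm is therefore a reasonable inference, but it is not stated.

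**2. Can the duplicate reading show a lean by arm?**

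Input from the protocol: about 350 patients, taken as 175 per arm (1:1 is an assumption). Other assumptions:
- The true use rate p is the same in both arms.
- Each reader misses 5% of events at random.
- In the video arm, a further share L is missed by both readers on the same charts.

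Formulas:
- Recorded rates: control pc = 0.95p; video pv = 0.95p(1 − L).
- Odds ratio: [pv/(1 − pv)] / [pc/(1 − pc)].
- Two-sided 5% rejection rate: Φ(d − 1.96) + Φ(−d − 1.96), with d = (pc − pv)/√[pc(1 − pc)/175 + pv(1 − pv)/175].
- Pooled kappa: with m the mean of pc and pv, the readers disagree on a share 2(m − 0.95m) = 0.10m of charts, and chance disagreement is 2m(1 − m). So kappa = 1 − 0.05/(1 − m).

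Worked case, p = 0.30 and L = 0.20:
- pc = 0.285 and pv = 0.228.
- Odds ratio = (0.228/0.772)/(0.285/0.715) = 0.74.
- d = 0.057/0.0466 = 1.22, so the rejection rate is 23%.
- m = 0.2565, so kappa = 1 − 0.05/0.7435 = 0.93.

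| L (p = 0.30) | pv | Odds ratio | Rejection rate | Kappa |
|---|---|---|---|---|
| 0 | 0.285 | 1.00 | 5% | 0.93 |
| 10% | 0.257 | 0.87 | 9% | 0.93 |
| 20% | 0.228 | 0.74 | 23% | 0.93 |
| 30% | 0.200 | 0.63 | 47% | 0.93 |

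At L = 20%, the same formulas give an odds ratio of 0.76 and a rejection rate of 16% for p = 0.20, and 0.71 and 32% for p = 0.40.

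**What agreement can show.** If the extra misses are independent between readers, pooled kappa at p = 0.30 falls to 0.87, 0.82 and 0.78 for L = 10%, 20% and 30%. A pooled figure still does not say which arm is affected. Splitting by arm does not help when the lean is shared: at L = 20%, kappa is 1 − 0.05/0.772 = 0.94 in the video arm and 1 − 0.05/0.715 = 0.93 in the control arm.

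It does help once the second reader is masked and so does not share the lean. In the video arm at L = 20%:
- The readers record 0.228 and 0.285, and both find 0.30 × 0.80 × 0.95² = 0.2166.
- Observed agreement = 1 − (0.228 + 0.285 − 2 × 0.2166) = 0.920.
- Chance agreement = 0.228 × 0.285 + 0.772 × 0.715 = 0.617.
- Kappa = (0.920 − 0.617)/(1 − 0.617) = 0.79, against 0.93 in the control arm.

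**After the fix.** With masked readers L = 0, which is the first row of the table.

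**The case against.** **Two safeguards are named.** A reader might infer that duplicate-chart agreement is the only one. It is not: the form is named in the sentence before it. The form limits discretion, but it does not mask the arm.

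**The text does not tie abstractors to this outcome.** A reader might infer that the protocol hands healthcare use to staff who know the arm. The Data and safety monitoring plan speaks of chart data in general and does not name this outcome. Extraction by the data-analytics group is neither stated nor excluded. Knowledge of the arm is inferred from the unblinded design and the overlapping roles. This stands, and it is why the point asks for a statement and a safeguard and does not allege that bias will occur.

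**This is silence in a condensed article.** Access rights and abstraction manuals often sit elsewhere, and the appendix listing the data elements is not shown. This has force. But the article does not leave abstraction quality to another document: it names the measures and presents the duplicate reading as the guarantee of quality. Using that reading for inter-observer variability is correct. It does not cover differential ascertainment.

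**The size is not anchored.** True. Nothing in the documents makes a gap of 20% or 30% likely, and visits found in a record on a set form are fairly objective. The figures show that the check is insensitive. They do not predict the bias.

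**Little depends on it.** The outcome is one of several secondary ones, and the hypotheses concern only readiness and confidence. This also stands.

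**Conclusion.** The point holds as an avoidable weakness in how one secondary outcome is ascertained. The form and the duplicate reading cannot reveal a lean shared by both readers, and nothing in the article masks abstractors.

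The size is unknown. Under the assumed rates of 20% to 40%, a shared 20% lean would give a spurious odds ratio of 0.76 to 0.71 and a false-positive rate of 16% to 32% with no warning from kappa. At a 30% use rate, a 10% lean would raise the false-positive rate only from 5% to 9%. The direction was chosen for illustration and could be the reverse. If the outcome is in fact extracted automatically and identically in both arms, saying so settles the matter.

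The documents do not support a reading that the trial's main conclusion is at risk, because the primary outcome is patient-reported and does not pass through chart abstraction.

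**What to change.** In the Data and safety monitoring plan, state that healthcare use outside the clinic at 30 days and 6 months is obtained in one of two ways:

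1. By automated extraction applied identically to both arms; or
2. By abstractors who work from a list holding only study ID, record number and index-visit date. REDCap allocation and survey fields stay hidden until abstraction is locked, and each chart goes to a team member who did not enrol, treat or follow up that patient.

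Hiding the REDCap fields is not enough alone, because it does not mask someone who ran that patient's visit.

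The second reader of duplicate charts should be masked to the arm and to the first reading, and agreement should be reported by arm.

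The cost is a user-rights setting, a few sentences and some scheduling of chart assignments within the existing team. An occasional chart note may still reveal the arm.

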## Regulatory requirements

### Informed consent

All patients will be consented. Informed consent will be obtained before the randomization of subjects. If they approve, the research team member will administer the informed consent form within the supplementary information of this protocol.

Those who approve to watch the interactive video will be given a QR code to watch on their smartphone or a tablet with a link to the video, which the patient or the research team member may start.

### Participant privacy

Subject confidentiality will be maintained using a randomly generated participant identification number/code. The participant identification number will be stored with the patient’s identifying information, such as name and room number, for verification purposes. Identifying information will be kept in a password-protected, secure REDCap file on a password-protected server. Such information will only be accessible to the research team trained in research ethics (CITI training) and HIPAA compliance.

Using personally identifiable data is necessary to determine eligibility, abstract chart data, and follow up with patients. All patient information collected will be stored in a password-protected secure server using REDCap and only accessed when necessary by authorized research associates.

### HIPAA

All parties involved shall maintain the confidentiality of PHI to ensure compliance with privacy regulations, including the Health Insurance Portability and Accountability Act of 1996 (HIPAA). The study team will consist of only personnel trained in research ethics (CITI training) and HIPAA compliance.

Patient eligibility will be determined by screening in Epic EHR. We will request a waiver of HIPAA authorization for this portion of the study and access to the patient’s medical record.

### Unanticipated problems and adverse events

This project is considered to be minimal risk, such as loss of protected health information and discomfort of answering questions. Any unanticipated problems will be promptly reported to the PI, project’s research coordinator, and the IRB. If necessary, the project will be discontinued until resolution in consultation with Trinity Health, Ann Arbor IRB. This trial involves preventive health education and does not involve any interventions that carry a risk of physical harm. Therefore, provisions for ancillary and post-trial care related to trial participation, as well as compensation for harm, are not applicable.

## Limitations and assumptions

Since this is planned as a single-institution study, this will limit generalizability.
